#### Paediatric Index of Mortality

The Paediatric Index of Mortality (PIM3) is used to provide an estimate of mortality risk among children admitted to paediatric intensive care [13]. The PIM3 consists of 10 variables that should be collected within one hour after arrival at the PICU. The PIM3 score consists of physiological variables and categorical variables that classify patients based on the reason for admission, the use of mechanical ventilation and diagnostic risk data [13]. It is not meant to be used as a marker for the severity of illness of individual patients; however, like other mortality prediction models, it has been used to evaluate the risk of mortality when registering patients in clinical trials and as a tool for monitoring the quality of intensive care [13]. Thus, we also use invasive ventilation and inotropes as markers for the severity of illness.

### Sample size

A power calculation was made based on accessible data from 2013 from the departments that are currently employing PEWS models. The available preliminary data showed 154 unplanned transfers to the PICU out of 10,000 admissions. With a power of 80%, a 5% significance level and an expected 30% reduction in the number of transfers to intensive care, we would have to include 7112 children in each group. The total available study population is 26,800 children annually.

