**Methods/design:**

This is a multicentre, randomised, controlled clinical trial where children are allocated to one of two different PEWS models. The study involves all paediatric departments and one emergency department in the Central Denmark Region. The primary outcome is unplanned transfer to the paediatric intensive care unit or transfer from regional hospitals to the university hospital. Based on preliminary data, 14,000 children should be included to gain a power of 80% (with a 5% significance level) and to detect a clinically significant difference of 30% of unplanned transfers to intensive care or from regional hospitals to the paediatric department at the university department. A safety interim analysis will be performed after inclusion of 7000 patients.

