### Outcomes

The primary outcome is the sum of unplanned transfers to the PICU and transfers from regional hospitals to the university hospital or the number of deaths. Transfers from regional hospitals to the paediatric department at the university hospital are equated with transfers to the PICU; children who need intensive care at the regional hospitals will be transferred to the paediatric department at the university hospital to ensure proximity to the PICU.

The secondary outcomes are as follows:Paediatric Index of Mortality scoreSeverity of illness during PICU stay based on invasive ventilation and inotropesLength of hospital stayLength of PICU stay

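### The 80% power is not supported for the primary outcome: the planning rate is described as PICU transfers, the power is claimed for a wider composite, and what the 154 events include is not stated

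*Protocol article*

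**What the plan says.** Four places in the protocol article describe the outcome that the trial is sized for or tests, and they differ.

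- **Sample size.** The planning rate is given as: "The available preliminary data showed 154 unplanned transfers to the PICU out of 10,000 admissions". The effect is an "expected 30% reduction in the number of transfers to intensive care". With 80% power and a 5% level, the section concludes that "we would have to include 7112 children in each group". Regional transfers and deaths are not mentioned.
- **Abstract, Methods/design.** The 80% power from 14,000 children is claimed for a two-part outcome: "detect a clinically significant difference of 30% of unplanned transfers to intensive care or from regional hospitals to the paediatric department" (that of the university hospital).
- **Outcomes.** Here the main endpoint is defined as follows: "sum of unplanned transfers to the PICU and transfers from regional hospitals to the university hospital or the number of deaths". The section adds that a regional-to-university transfer counts as equivalent to a PICU transfer, because regional children who need intensive care are moved to be near the PICU.
- **Statistical methods.** The primary logistic regression is described for unplanned PICU admissions only.

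The article gives no event rate for regional transfers, deaths or the composite. It does not say whether the 154 events include regional transfers.

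**The concern.** A power statement belongs to one outcome, with one control rate and one assumed effect. Here the rate and effect are described for transfers to intensive care, and the resulting power is claimed for a wider outcome. Adding a component changes the control rate. It also changes the overall relative reduction, unless the new component responds to the same degree. The two changes can pull power in opposite directions, so the 80% cannot simply be carried across.

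This is not a detail that a journal article leaves to a fuller document. The article states the planning event, the effect and the power, and attaches them to differently described outcomes. At stake is how the result is read: a non-significant primary result would be judged against a power that has not been shown for that outcome.

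**Working it through.** **Inputs.** From the article: control rate 154/10,000 = 1.54%; reduction 30%; power 80%; level 5%; 7112 per group or 14,000 in total; 1:1 allocation (Allocation section), hence 7000 per arm. Assumed: a two-sided test, because sidedness is not stated. All composite rates below are also assumptions, because the article gives none.

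**Step 1: the plan's own figure.** With p1 = 0.0154 and p2 = 0.7 × 0.0154 = 0.01078, the difference is d = 0.00462 and the mean rate is p̄ = 0.01309.

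n per group = [1.960 √(2p̄(1−p̄)) + 0.8416 √(p1(1−p1) + p2(1−p2))]² / d²

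= [1.960 × 0.16074 + 0.8416 × 0.16071]² / 0.00462² = (0.4503 / 0.00462)² ≈ 9500.

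The stated 7112 is not reproduced. A continuity correction gives 9929. A one-sided 5% test gives 7483, or 7910 with the correction. By back-calculation (uncorrected formula), 7112 corresponds to a control rate of about 2.05% with a 30% reduction, or to a reduction of about 34% from 1.54%. The article states neither. Also, 2 × 7112 = 14,224, not 14,000.

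**Step 2: power if the 154 already includes regional transfers.** The rate for the two-part outcome is then 1.54%.

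Power = Φ{[d − 1.960 √(2p̄(1−p̄)/n)] / √((p1(1−p1) + p2(1−p2))/n)}

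At n = 7000: (0.00462 − 1.960 × 0.0019212) / 0.0019208 = 0.445, and Φ(0.445) = 67%. At n = 7112 it is 68%. With the continuity correction the figures are about 64% and 65%.

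**Step 3: power if it does not.** The same formula at 7000 per arm:

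| Assumption | Control rate | Other arm | Overall reduction | Power |
|---|---|---|---|---|
| 30% reduction throughout | 2.0% | 1.40% | 30% | 78% |
| 30% reduction throughout | 2.08% | 1.456% | 30% | 80% |
| 30% reduction throughout | 2.5% | 1.75% | 30% | 87% |
| Regional adds 0.5 points and falls 30% | 2.04% | 1.428% | 30% | 79% |
| Regional adds 0.5 points and falls 15% | 2.04% | 1.503% | 26% | 67% |
| Regional adds 0.5 points and does not fall | 2.04% | 1.578% | 23% | 54% |

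The last row is a worst case at that rate: regional transfers are all additional to PICU transfers and do not respond at all. Deaths are left out of every row. The Discussion calls the rate of in-hospital arrest or death low in this age group, so they are unlikely to move these figures much.

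**The case against.** The strongest reply is that the article uses PICU transfer as shorthand for its whole primary outcome. Outcomes makes regional and PICU transfers equivalent, Statistical methods uses the short form for the primary analysis, and the Discussion says that transfer to the PICU was the chosen marker. On that reading the 154 is already the two-part count and the Sample size section is only loosely labelled. This stands as a possibility. A reader might infer that the trial was sized for PICU transfers alone, but the article does not establish that: the equivalence defines the trial's outcome and does not say how the 2013 data were counted. Nor does the shorthand rescue the 80%, because a rate of 1.54% gives about 67%.

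A reader might also infer that 80% is at least right for PICU transfers. It is not: with the stated inputs Step 2 applies to them as well.

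A third tempting inference is that the wider outcome costs power. The article does not support that either. With the same 30% reduction, a more frequent outcome has more power than the 67% at 1.54%. The 54% requires that regional transfers neither overlap with PICU transfers nor respond, whereas the Hypothesis section expects them to fall.

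Finally, the practical consequence is limited. Confidence intervals will show the precision achieved, recruitment is nearly complete (12,000 of 14,000 by January 2017), and nothing shows that the monitoring committee relied on the 80%.

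**Conclusion.** The point holds in this form: no reading of the article supports 80% power for the primary outcome from what it states. If the 154 includes regional transfers, power at 7000 per arm is about 67%. If it does not, power for the composite was not derived. It could lie above or below 80%, and the direction cannot be told from the article. With a 30% reduction throughout, 80% is reached only at a composite rate of about 2.08%, which the article does not give.

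These figures assume a two-sided 5% test, the normal approximation without continuity correction, and no contribution from deaths. The defect lies in the stated justification for the sample size. It does not show that the trial is underpowered for its composite.

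**What to change.** 1. Use one definition of the primary outcome in the abstract, Outcomes, Sample size and Statistical methods, and say whether deaths count.
2. State in Sample size which events the 154 counts. If regional transfers are included, relabel the figure.
3. Take the event rate for that outcome from the 2013 data. Failing that, use an arm-blind pooled count of reviewed events among the children already randomised.
4. In the abstract and Sample size, replace the 80% with the recomputed power, or the smallest detectable reduction, at 14,000 children. Name the formula and the sidedness, and reconcile 7112 per group with 14,000.

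The cost is one rate, one recalculation and a few reworded sentences. The 2013 route is cheaper: a pooled trial count needs the two-researcher record review that excludes planned transfers, and because the research team is unblinded, the count would have to be assembled without arm labels. Enrolment does not change. The downside is that the stated power may become less favourable.

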## Methods/design

### Study setting

The study is ongoing in four paediatric departments, four paediatric emergency and assessment units, one emergency department and a specialised paediatric unit for children with neurological illness in the Central Denmark Region. Including both a university hospital and several regional hospitals helps ensure the highest possible diversity in the population and strengthens the study’s generalisability. The participating departments are listed on the project homepage (www.pews.dk). None of the participating hospitals had been working with any kind of PEWS model prior to this study.

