### Allocation

The departments will all have access to a web-based randomisation programme, Trialpartner. Each patient receives his or her own randomised number. If a patient is readmitted during the inclusion period, observation will continue based on the result of the initial randomisation. Consecutive eligible patients are randomly allocated with a 1:1 ratio to one of the two PEWS tools. There is no stratification at the patient or institution level.

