### Statistical methods

Statistical analysis will follow the modified intention-to-treat principle [14]. Analysing the primary outcome, logistic regression of PEWS on unplanned PICU admissions will be performed to determine odds ratios (ORs) and 95% confidence intervals (CIs). The analysis will be adjusted for age. In the secondary outcome analysis, categorical data will be analysed using the chi-square test. Continuous data that are not normally distributed will be analysed using the Mann-Whitney *U* test. A *p* value <0.05 is considered significant.The two PEWS tools will also be evaluated using sensitivity, specificity and the receiver operating characteristic curve. In this study, sensitivity is the ability of the PEWS tool to correctly identify children at risk of an unplanned transfer to the PICU. Specificity is the ability of the tool to demonstrate a low score among children who are not at risk of an unplanned transfer to the PICU; thus, a low specificity indicates a high rate of false positives. Sensitivity and specificity will be calculated to measure the validity of the tools and the most predictive score for an unplanned transfer to the PICU. As the PEWS must be able to identify children at risk of acute life-threatening conditions and provide a ‘window’ for intervention, data analysis will stop one hour prior to the occurrence of the acute life-threatening condition to avoid overestimating the effect of the PEWS.

Descriptive statistics will be calculated to describe baseline variables and clinical characteristics. The descriptive analysis will be summarised as percentages, with median and interquartile ranges provided for continuous variables. STATA version 10 will be used for the analyses.

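### The 7112 children per group does not follow from the stated inputs, which require about 9500; at the stated 1.54% rate, 14,000 children give about 67% power for a 30% reduction, not 80%

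*Protocol article*

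**What the plan says.** The Sample size section of the protocol article gives both the inputs and the result.

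- Base rate: "The available preliminary data showed 154 unplanned transfers to the PICU out of 10,000 admissions".
- Effect: "an expected 30% reduction in the number of transfers to intensive care".
- Error rates: "With a power of 80%, a 5% significance level".
- Result: "we would have to include 7112 children in each group".

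The Methods/design part of the abstract gives the total: "14,000 children should be included to gain a power of 80% (with a 5% significance level"). It ties this to a 30% difference, there described as covering both transfers to intensive care and transfers from regional hospitals. Under Allocation, children are "randomly allocated with a 1:1 ratio to one of the two PEWS tools", so 14,000 means 7000 per group.

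The sidedness of the test is not stated. Statistical methods plans "odds ratios (ORs) and 95% confidence intervals (CIs") and a 0.05 threshold for p values, which points to a two-sided test. Outcomes defines the primary outcome as unplanned PICU transfers together with transfers from regional hospitals to the university hospital, or deaths.

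**The concern.** The paragraph can be checked from its own contents, and its result is about a quarter smaller than its inputs require (7112 / 9500 = 0.75). The abstract then repeats the 80% for a slightly smaller total.

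What is at stake is how a null result would be read. An 80%-powered trial misses a true effect of the planned size one time in five. If the control rate is the stated 1.54%, this trial would miss a true 30% reduction about one time in three. A non-significant comparison would then be taken as stronger evidence of no difference between the two PEWS models than the design can support.

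**Working it through.** **Inputs.** Control rate p1 = 154/10,000 = 0.0154 (Sample size). Reduced rate p2 = 0.7 x 0.0154 = 0.01078. Difference d = 0.00462. Mean rate pm = 0.01309. Power 80% (z = 0.8416). Significance 5%, taken as two-sided (z = 1.9600). Allocation 1:1.

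**Sample size, two-sided.**

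n = [1.9600 x sqrt(2 pm(1-pm)) + 0.8416 x sqrt(p1(1-p1) + p2(1-p2))]^2 / d^2

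- sqrt(2 x 0.01309 x 0.98691) = 0.16074; times 1.9600 = 0.31504
- sqrt(0.0154 x 0.9846 + 0.01078 x 0.98922) = 0.16071; times 0.8416 = 0.13525
- n = (0.45030)^2 / (0.00462)^2 = 0.202769 / 0.0000213444 = 9500 per group, 19,000 in total

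**Attempts to reproduce 7112 from the stated inputs** (per group):

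| Method | Two-sided 5% | One-sided 5% |
|---|---|---|
| Pooled variance | 9500 | 7483 |
| Unpooled variance | 9498 | 7481 |
| Arcsine | 9428 | 7426 |
| Log odds ratio | 9601 | 7563 |
| Continuity-corrected | 9929 | 7910 |
| 30% read as an odds ratio of 0.7 (pooled) | 9728 | 7663 |

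None gives 7112. The nearest, one-sided arcsine, is 4.4% above it, since 7426/7112 = 1.044.

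**Power at the planned size.** Power = Phi[(d x sqrt(n) - 0.31504) / 0.16071].

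- n = 7112: (0.38962 - 0.31504) / 0.16071 = 0.464, so 67.9%
- n = 7000: (0.38654 - 0.31504) / 0.16071 = 0.445, so 67.2% (64.4% with continuity correction)
- One-sided 5% at n = 7000: 77.6%, still short of 80%

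**What would give 80%.** These come from solving the same formulas.

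- Control rate held at 1.54%: a reduction of 34.2% at 7112 per group, or 34.5% at 7000.
- Reduction held at 30%: a control rate of 2.05% at 7112 per group, or 2.08% at 7000.

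**Sensitivity to the control rate** (assumed range; 30% reduction, 7000 per group, two-sided 5%):

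| Control rate | Power |
|---|---|
| 1.0% | 49% |
| 1.2% | 56% |
| 1.54% (stated) | 67% |
| 1.8% | 74% |
| 2.05% | 79% |
| 2.2% | 82% |
| 2.5% | 87% |

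**A possible origin.** Comparing 1.54% with a rounded 1.00%, with continuity correction, gives 7115. That is a 35% reduction (1 - 1.00/1.54 = 0.351). This is an inference; the article does not say so.

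**The total.** 2 x 7112 = 14,224, against 14,000 in the abstract. The gap of 224 children (1.6%) costs 0.7 percentage points of power (67.9% to 67.2%).

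**The case against.** The strongest objection is that 1.54% may not be the control-arm rate of the primary outcome. The composite takes in regional-to-university transfers and deaths. If the 154 events leave these out, the composite rate in the same data would be at least as high, and power would rise with it. This stands in part. A reader might infer that the trial simply has 67% power, but the documents support that figure only at the stated rate. The objection does not rescue 7112, because the paragraph derives that number from 1.54% and no other rate is given.

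A reader might also infer that the 1.54% counts PICU transfers only. The wording in Sample size suggests it, but Outcomes treats regional-to-university transfers as equivalent to PICU transfers, so the 154 may already include them. The article does not settle this.

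A third tempting reading is a contradiction over prior PEWS use. Sample size draws its 2013 data from departments described as now using PEWS, while Study setting says "None of the participating hospitals had been working with any kind of PEWS model prior to this study". The documents do not support a conflict. Recruitment began in November 2014, so these can be departments that use PEWS because they joined the trial, with data from before it.

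If the rounding explanation is right, the effect size is the misstated item, and power for a 35% reduction at 7000 per group is 81% without continuity correction. The printed 30% would still be wrong.

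Finally, the planned confidence intervals will show how imprecise a null result is. That lessens the harm but does not make the stated power correct.

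**Conclusion.** The point holds in conditional form. Without further assumption, 7112 per group does not follow from the printed inputs by any of the methods tried. A two-sided test needs about 9500 per group, about 34% more than stated (9500/7112 = 1.34), and a one-sided test about 7480.

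The shortfall in power, about 13 percentage points (80% stated, 67% computed), rests on two assumptions: a two-sided 5% test, and a control rate for the primary outcome equal to the stated 1.54%. Power for the composite as defined is unknown, because the article gives no rate for it. An unseen analysis plan does not explain the mismatch, since the inputs and the result are printed together. The difference between 14,000 and 14,224 is minor, but it too lowers power.

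**What to change.** Correct the Sample size section and the abstract together. No extra patients and no change to the analysis are needed.

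1. State that 14,000 children give about 67% power for a 30% reduction from 1.54%, or 80% power for a reduction of about 34-35%. Give the sidedness and formula used.
2. Make the total and the per-group figure agree (14,000 against 14,224).
3. Say which events the 154 per 10,000 covers: PICU transfers alone, regional-to-university transfers as well, or the full composite including deaths.
4. Optionally, restate the detectable reduction from the pooled composite rate per child, taken across both arms. The trial is open-label and its by-arm interim analysis has been done, so the condition should be that this is fixed before the final comparison by arm. It also has to wait for the planned two-researcher review that removes planned transfers.

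Steps 1 to 3 cost a rewritten paragraph and one abstract sentence, and the stated power becomes less favourable. Step 4 adds one pooled count once the record review is complete.

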### Recruitment

Recruitment of patients started on 12 November 2014 and is ongoing. As of January 2017, 12,000 patients have been randomised into one of the two arms. Inclusion of the final 2000 patients is expected to be reached by the end of March 2017 (Fig. 1).

**Fig. 1 Fig1:**
[figure not shown]
Inclusion rate

### Allocation

The departments will all have access to a web-based randomisation programme, Trialpartner. Each patient receives his or her own randomised number. If a patient is readmitted during the inclusion period, observation will continue based on the result of the initial randomisation. Consecutive eligible patients are randomly allocated with a 1:1 ratio to one of the two PEWS tools. There is no stratification at the patient or institution level.

### Sequence generation

A data manager who is not involved in recruiting patients devised the randomisation procedure. Healthcare professionals in the participating departments will enrol and assign patients to the randomised PEWS model in the electronic patient chart. Patients, clinicians and the research team will not be blinded.

### Data collection and management

The overall SPIRIT study schedule is illustrated in Fig. 2.

**Fig. 2 Fig2:**
[figure not shown]
SPIRIT study schedule

Separate interactive registration modules in the electronic patient chart were designed for each of the two PEWS models. The study data are extracted from the electronic patient charts. Thus, healthcare professionals in each department are responsible for data collection and data entry into the electronic patient chart as well as for obtaining consent from the parents.

For each patient included in the study, the following data are collected:Baseline demographics: child’s age, gender, pre-existing conditions, diagnostic category (cardiac, post-surgical, neurological, respiratory, infection, hydration)Clinical characteristics: discharge diagnosis, triage level at admission, time of day of critical event (day, evening, night)PEWS parameters and temperature in the 24 hours preceding transfer to the PICU, ending one hour before transfer to the PICUFrequency of PEWS and temperature measurements during the last 24 hours prior to transfer to the PICU, ending one hour before transfer to the PICUData from PICU: PIM3 scoreOutcome data: unplanned transfer to the PICU or university hospital, length of hospital stay, length of PICU stay

Transfers to the PICU and transfers from regional hospitals to the university hospital will be identified from the electronic patient charts. Two researchers will review each of these medical records to exclude planned transfers. These are transfers that are elective or planned in advance, transfers coming directly from the operating room and transfers in which the need for PICU care was due to the need to recover from sedation.

This trial will follow the recommendations from the Consolidated Standards of Reporting Trials (CONSORT) statement for non-pharmacological treatment interventions.

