### Hypothesis

The hypothesis is that the Central Denmark Region PEWS is superior to the Bedside PEWS in terms of reducing hospitalised children’s unplanned transfers to the intensive care unit and transfers from regional hospitals to the university hospital due to clinical deterioration requiring proximity to a paediatric intensive care unit (PICU).

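### The two researchers who exclude planned transfers from the primary outcome are not masked to allocation, although part of that exclusion needs judgement and the review could be masked

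*Protocol article*

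**What the plan says.** All places are in the protocol article.

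- **Outcomes,** where the endpoint definition reads: "The primary outcome is the sum of unplanned transfers to the PICU and transfers from regional hospitals to the university hospital or the number of" (the sentence ends by naming fatal cases). Transfers are therefore the main component of the endpoint.
- **Data collection and management, source:** "Transfers to the PICU and transfers from regional hospitals to the university hospital will be identified from the electronic patient charts".
- **Data collection and management, filter:** "Two researchers will review each of these medical records to exclude planned transfers".
- **Data collection and management, criteria:** "These are transfers that are elective or planned in advance, transfers coming directly from the operating room and transfers in which the need for PICU" (the sentence goes on to give recovery after sedation as the reason in the third category).
- **Data collection and management, chart layout:** "Separate interactive registration modules in the electronic patient chart were designed for each of the two PEWS models".
- **Sequence generation:** "Patients, clinicians and the research team will not be blinded".
- **Hypothesis:** "The hypothesis is that the Central Denmark Region PEWS is superior to the Bedside PEWS".

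The article nowhere exempts the two reviewing researchers from the open design.

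**The concern.** A transfer counts towards the primary outcome only if the two researchers do not exclude it. They belong to a team that is declared unblinded and has a directional hypothesis, and the chart they read shows the arm. If borderline transfers are called planned somewhat more often in one arm, the odds ratio moves even when the two models perform alike. The age-adjusted logistic regression under Statistical methods does not correct for this. Masking ward care is not practicable in this trial, but masking a retrospective record review is.

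**Working it through.** **1. Can the reviewers know the arm?** The statement under Sequence generation is general and covers the research team. The filter under Data collection and management is applied by researchers to medical records, and the transfers come from the electronic charts, where each model has a separate module. Together these leave the reviewers unmasked, by inference from a general statement; no sentence describes the review itself as open. The module is the decisive cue. A blood pressure entry alone is weaker evidence, because the Background makes it optional in the regional arm and Table 2 prompts for it under both models.

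**2. Is there judgement to influence?**

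| Exclusion category | Nature |
|---|---|
| Elective or planned in advance | Elective status is often documented; advance planning may have to be read from notes |
| Directly from the operating room | Largely factual |
| PICU need due to recovery from sedation | Requires a judgement of cause |

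Only borderline records in the first and third categories are exposed. The article gives neither their number nor the number of planned transfers.

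**3. What size could it have?** No document figure describes differential exclusion, so what follows is an illustration.

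Inputs:
- Event rate p = 154/10,000 = 0.0154, from Sample size: "The available preliminary data showed 154 unplanned transfers to the PICU out of 10,000 admissions". This covers PICU transfers only, whereas the primary outcome also contains regional-to-university transfers and deaths. The event count for the full endpoint may therefore differ.
- n = 7000 per arm, from the Abstract's 14,000 with 1:1 allocation. Expected events are 7000 × 0.0154 = 107.8, about 108 per arm.
- Assumptions: no true effect, a two-sided 5% test (the article does not state the sidedness), and a share m of truly unplanned transfers wrongly excluded in one arm with no matching error in the other.

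Formulas, with p2 = p(1 − m), d = p − p2 and p̄ = (p + p2)/2:
- OR = [p2/(1 − p2)] / [p/(1 − p)]
- SE0 = √[2p̄(1 − p̄)/n]; SE1 = √{[p(1 − p) + p2(1 − p2)]/n}
- Rejection probability = Φ[(d − 1.96·SE0)/SE1] + Φ[(−d − 1.96·SE0)/SE1]

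For m = 10%:
- p2 = 0.01386, d = 0.00154, p̄ = 0.01463, SE0 ≈ SE1 ≈ 0.00203.
- The two arguments are −1.201 and −2.719.
- The probabilities are 0.1148 + 0.0033 = 0.118.

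| m (assumed) | Records affected | Expected OR | False-positive rate |
|---|---|---|---|
| 0% | 0 | 1.00 | 5.0% |
| 5% | about 5 | 0.95 | 6.6% |
| 10% | about 11 | 0.90 | 11.8% |
| 15% | about 16 | 0.85 | 21.1% |

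Exclusion errors that are equal in both arms would leave the false-positive rate at about 5%; that is what masking aims at. The planned sample size plays no part in this point.

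**The case against.** The strongest reply is that the criteria are written in advance, two people apply them, one category is close to factual and elective status is often on record. That stands. It narrows the exposure to borderline records but does not remove it.

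A second reply is that the 5% to 15% range has no source in the documents and treats all 108 events as open to reclassification. That also stands. At 10%, about 11 unplanned transfers must be wrongly excluded in one arm only. Without the number of borderline records, nobody can say from the article whether that is plausible.

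Four stronger readings may tempt a reader, and the documents do not support them:
- *The result is biased.* The article shows an avoidable risk, not that differential exclusion took place.
- *The damage cannot be repaired.* It largely can. All transfers are identified from the charts before any exclusion, so they can be analysed without the reviewers' decisions, and the charts can be reclassified masked.
- *A shift of 27 events, 108 against 81, would alone produce significance.* That means losing 27/108 = 25% of one arm's events, outside the range above. The uncorrected chi-square p is 0.048, but the continuity-corrected and Fisher exact values are both about 0.057.
- *The article should have specified independent reading, a rule for disagreement and agreement statistics.* An article commonly leaves these to the full protocol, so their absence is no finding. The open status of the research team is different, because the article states it.

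**Conclusion.** The point holds as a risk in the stated design: a partly judgemental filter on the primary outcome is applied by researchers who are not masked, from records that show the arm. The conclusion rests on reading the general blinding statement as covering the two reviewers, which the text supports because it makes no exception.

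The size is unknown. The illustrative odds ratios of 0.95 to 0.85, with false-positive rates of about 7% to 21%, depend on the assumed one-sided differential, the PICU-only event rate and 7000 per arm. They show that with about 108 events per arm, roughly a dozen one-sided decisions would matter; they do not estimate what happened. The change should be made because it is inexpensive and the step remains repairable.

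**What to change.** - Amend Sequence generation and Data collection and management so that the same two researchers classify each transfer from an extract without the allocation and the PEWS module, and lock the classification before it is linked to arm. Deaths need no such review, since they involve no planned-or-unplanned decision.
- Repeat the classification masked for any records already reviewed. The article reports that the interim comparison of transfers has been done, so some may have been; it does not say.
- Add a sensitivity analysis of all identified transfers, planned and unplanned. It dilutes a true effect but does not depend on the reviewers, so it shows whether the result rests on the exclusions.

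**Cost:** some data-manager time to prepare extracts. At 1.54% and 7000 per arm, about 2 × 108 = 216 unplanned transfers would be expected with no effect, or about 108 + 75 = 183 under the planned 30% reduction, plus planned transfers whose number is not given. No extra reviewers and no change to patient care are needed.

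**Limits:** masking will fail where free-text notes reveal the arm, and it cannot remove bias in the unblinded clinicians' decision to transfer.
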